#### Operationalization of the indices.

To ensure transparency and replicability, each index will be constructed according to clear theoretical and statistical criteria, as follows:

Income and Livelihood Diversification Index (ILDI): formative index calculated using the Herfindahl-Hirschman formula ($\text{1}-\sum {pi}^{\text{2}}$) [30] based on the relative shares of agricultural, extractive, and non-agricultural income. It will not be evaluated by Cronbach’s alpha but described statistically.Climate Adaptation Practices Index (CAPI): reflective index, constructed from the standardized sum of reported adaptation practices (e.g., irrigation, resistant varieties, collective work). Internal consistency will be assessed by Cronbach’s alpha [31] (α≥0.7) and, when appropriate, by confirmatory factor analysis.Bioeconomy Engagement Index (BEI): formative ordinal variable, with increasing levels of engagement in bioeconomy value chains (0: no participation; 1: primary production; 2: processing; 3: processing + certification/market differentiation). Higher values indicate greater household-level involvement. For multilevel analyses, the BEI will be used primarily as a level-1 predictor (household-level) to examine associations with income, adaptive capacity, and adoption of mitigation/adaptation practices. To explore community-level patterns, the BEI will also be summarized at the settlement level using the mean or distribution of household scores (e.g., proportion of households at each engagement level). These aggregated measures will be used as level-2 contextual variables when relevant for hypotheses concerning settlement-level dynamics (e.g., HP5).Climate Vulnerability Perception Scale (CVPS): reflective scale, constructed as the average of Likert-type items (1–5) capturing perceptions of climate risk (drought, flood, crop loss, food insecurity). Internal consistency will be assessed by Cronbach’s alpha (α≥0.7) and unidimensionality by CFA.Municipal Climate Vulnerability Index (MCVI): formative index based on indicators of exposure (climate), sensitivity (e.g., agricultural dependence, poverty), and adaptive capacity (e.g., education, policy access). It will be constructed from standardized indicators (z-scores) and aggregated through PCA. PCA adequacy indicators (KMO>0.6) and variance explained by the first component will be reported.

Each index will be statistically validated, described in terms of distribution, central tendency, and dispersion, and interpreted according to its reflective or formative nature.

#### Qualitative primary data analysis.

Transcriptions of interviews and focus groups will be analyzed using Braun and Clarke’s Reflexive Thematic Analysis [46] in six stages: (1) familiarization; (2) generation of initial codes; (3) search for themes; (4) review of themes; (5) definition and naming of themes; and (6) report production. This analysis will identify central themes related to local perceptions, barriers, facilitators, and understandings of climate change, adaptation, and bioeconomy.

All qualitative findings will be reported according to the COREQ guideline (or SRQR, where applicable), ensuring comprehensive documentation of data collection and analytic procedures.

#### Integration and triangulation.

In the final phase, the findings will be integrated following a sequential explanatory mixed-methods design (QUAN → QUAL) and a joint display triangulation framework [41]. The integration will be reported in accordance with the Good Reporting of a Mixed Methods Study (GRAMMS) framework and the Standards for Reporting Qualitative Research (SRQR) guidelines for the qualitative component.

A triangulation matrix will be constructed to systematically map convergences, complementarities, and divergences between quantitative, qualitative, and secondary data findings for each research objective and hypothesis. The matrix will define decision rules for interpreting relationships: (I) Convergence: Findings from different methods provide corroborating evidence for the same conclusion; (II) Complementarity: Findings from different methods elucidate distinct, non-overlapping aspects of a phenomenon, together providing a richer, more complete picture; (III) Discordance: Findings from different methods are contradictory or inconsistent. In such cases, we will re-examine the data and the assumptions of each method to propose potential explanations for the discrepancy (e.g., differences in perspective between managers and farmers, social desirability bias in surveys). (IV) Silence: An expected finding from one method is absent in the data from another method.

For example, a quantitative pattern of low adoption of a bioeconomy practice (QUAN) will be examined considering reported barriers in interviews (QUAL) and the (non)existence of supportive policies identified in secondary data. This synthesis will enable not only the identification of *what* occurs but also *why* and *how* adaptation and resilience processes unfold.

#### Handling of missing data.

The strategy for handling missing data will be determined by its mechanism and extent. During data collection, digital forms with mandatory field checks will minimize inadvertent missingness. Interviewers will be trained to probe for reluctant or “don’t know” responses. Prior to analysis, we will generate a missingness pattern report. Little’s Missing Completely at Random (MCAR) [47] test will be used to inform the choice of handling method, though we will primarily assume data is Missing at Random (MAR).

Our primary analysis will use a Full Information Maximum Likelihood (FIML) estimation within the mixed-effects models (lme4 package in R). FIML uses all available data points without discarding partial cases and provides unbiased estimates under the Missing at Random (MAR) assumption.

To assess the robustness, we will conduct sensitivity analyses using Multiple Imputation (mice package in R). We will create 20 imputed datasets, including all model variables and auxiliary variables correlated with missingness. The multilevel structure will be respected during imputation using the 2lonly method, incorporating cluster means of level 1 variables as predictors. All model variables, plus auxiliary variables correlated with missingness (e.g., interview duration, interviewer ID), will be included in the imputation model. Results from the pooled imputed models will be compared with the primary FIML analysis.

In addition to primary data, we will assess and report missingness in all secondary datasets, including climate indicators, socioeconomic data, municipal plans, and budget information. For missing values in external data sources, we will apply appropriate strategies depending on the mechanism: (i) triangulation with alternative official databases when equivalent indicators exist, (ii) imputation of continuous variables using multilevel or time-series–based methods when justified, and (iii) explicit coding of structural missingness (e.g., municipalities with no climate plans or no identifiable climate-related expenditures). The extent and implications of missing secondary data will be documented in the Municipal Climate Vulnerability Index (MCVI) and in the construction of the Municipal Climate Engagement Typology (MCET), and sensitivity checks will be conducted to assess the robustness of results to these gaps.

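### The only robustness check on survey missing data shares the primary analysis's missing-at-random assumption, so for PH5 household income agreement between the two cannot rule out bias from income withheld because of its level

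*Protocol article*

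**What the plan says.** All of the following is in the protocol article.

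- **Assumption** (Handling of missing data): "we will primarily assume data is Missing at Random (MAR"). Little's test is to inform the choice of method.
- **Primary analysis** (same section): "Our primary analysis will use a Full Information Maximum Likelihood (FIML) estimation within the mixed-effects models (lme4 package in R"). The section adds that this "provides unbiased estimates under the Missing at Random (MAR) assumption".
- **Robustness check** (same section): "To assess the robustness, we will conduct sensitivity analyses using Multiple Imputation (mice package in R"). It is specified as "We will create 20 imputed datasets, including all model variables and auxiliary variables correlated with missingness", with interview duration and interviewer ID as example auxiliaries. It is read as follows: "Results from the pooled imputed models will be compared with the primary FIML analysis".
- **Source of missing answers** (same section): mandatory fields are meant to limit accidental gaps, and "Interviewers will be trained to probe for reluctant" and don't-know answers. No item is named.
- **Role of income**: Table 1 makes household income one of the PH5 outcomes. The section on confounding and sensitivity analysis gives the BEI–income association as its example of a key association. ILDI, the PH2 predictor, is computed from shares of agricultural, extractive and non-agricultural income (Operationalization of the indices).

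No scenario in which survey answers are missing not at random (MNAR) is stated.

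**The concern.** A robustness check is useful if it can disagree with the primary result when the primary assumption fails. Here the assumption most open to doubt is MAR, and both analyses make it. If better-off (or worse-off) households decline to report income even after education, assets, BEI and the other covariates are accounted for, both analyses fill the gap from the same observed relationship and are wrong in the same direction.

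The other checks do not reach this. Little's test concerns only missing completely at random. The sensemakr analysis concerns unmeasured confounders. The closing checks in the missing-data section concern municipal secondary data.

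At stake is how the comparison will be read. Close agreement on PH5 could be taken as reassurance about withheld income, which it cannot give.

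**Working it through.** The protocol gives no missing rate and no sensitivity parameter, so there is no figure to reproduce. The check is structural, followed by an illustration on assumed inputs.

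**1. Why the two analyses agree for an income outcome.** Each household supplies one income value. A household with no income value adds nothing to the mixed-model likelihood, so the primary fit is an available-case fit. Imputation under MAR draws missing incomes from the same observed relationship, so the pooled slope returns to that fit, apart from what the auxiliaries add.

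**2. PH5 illustration.** From the protocol: 600 families in 30 settlements, and ICC 0.10 from its listed range. Assumed: true slope 0.30 per BEI level; BEI shares 0.4/0.3/0.2/0.1; probability of withholding rising with income (logit slope 1.5 per SD); 20 imputations; 100 runs per scenario; settlement fixed effects standing in for the mixed model; no auxiliaries.

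| Missing | Full data | Available-case | MI under MAR | MI, imputed income +1 unit |
|---|---|---|---|---|
| 10% | 0.304 | 0.270 | 0.269 | 0.305 |
| 20% | 0.296 | 0.252 | 0.252 | 0.304 |
| 30% | 0.299 | 0.242 | 0.243 | 0.309 |

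The two MAR analyses differ by at most 0.001, while both fall about 0.03 to 0.06 below 0.30. The shifted imputation moves, so it exposes the dependence. When missingness depended only on an observed covariate, all four columns stayed between 0.289 and 0.306.

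The simulated income variance is 0.3² × 1.0 + 0.2² + 0.10 + 0.90 = 1.13, so the SD is 1.06 and the +1 unit shift is 1/1.06 = 0.94 SD.

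**3. Rough size as a two-group contrast.** Compare BEI 2–3 (group 1) with BEI 0–1 (group 0). Let *m* be the missing rate and *d* the departure of withheld income from its MAR prediction, in SD. Then bias = *d*₁*m*₁ − *d*₀*m*₀. With a common departure *d*, this is *d* × (*m*₁ − *m*₀), taken below in absolute size.

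- Low end: 0.3 × 0.05 = 0.015 SD.
- Middle: 0.55 × 0.10 = 0.055 SD.
- High end: 0.8 × 0.15 = 0.12 SD.
- Equal missing rates and equal departures: zero.

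With an assumed 25% in BEI 2–3 and clustering ignored, SE = √(1/(600 × 0.25 × 0.75)) = 0.094 SD. The ratios are 0.16, 0.58 and 1.27 SE. In the limiting case where BEI varies only between settlements, the design effect is 1 + 19 × 0.10 = 2.9, so SE = 0.094 × √2.9 = 0.16 and even 0.12 SD is 0.75 SE.

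**4. PH2 illustration (ILDI as predictor, true slope 0.30).** lme4 drops rows with a missing predictor, so the primary fit is complete-case. Results at 10/20/30% missing:

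| Missingness of ILDI depends on | Complete-case | MI under MAR |
|---|---|---|
| Observed outcome only (MAR) | 0.270/0.264/0.238 | 0.299/0.308/0.294 |
| ILDI itself only | 0.297/0.304/0.290 | 0.301/0.309/0.294 |
| Both ILDI and outcome | 0.234/0.199/0.172 | 0.253/0.222/0.201 |

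In the first row the comparison does its job. In the second there is no material bias. Only in the third does imputation stay clearly below 0.30.

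**The case against.** **This is a journal article, and MNAR scenarios are often left to an analysis plan.** That would answer a complaint about missing detail. The article, however, does name its robustness check and how it will be read, and the point is that this check does not probe the assumption it accompanies. A reader might infer that the authors present imputation as a test of MAR. They do not say so; they say only that it assesses robustness.

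**The comparison is not empty.** This stands. The imputation model adds auxiliaries, so its MAR condition is somewhat weaker than the primary one. The simulated agreement to 0.001 had no auxiliaries and is therefore closer than the study may see. A reader might infer that the comparison could never show anything, or that PH2 is as exposed as PH5. The PH2 results contradict both.

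**Income refusal is inferred.** This also stands. The protocol foresees reluctant and don't-know answers without saying to what, and the questionnaire is not shown. Income is a reasonable candidate, not a stated one. Income is not one of the four named primary outcomes either, although the protocol itself singles out BEI–income as a key association.

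**The size is assumed.** Correct. A reader might infer that the bias would exceed one standard error. That holds only near the top of an assumed range, and only with a standard error that ignores clustering.

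**Conclusion.** The point holds for PH5 household income. The stated check cannot expose bias from income withheld because of its level, and no other stated analysis does. For PH2 it holds only in reduced form: the comparison can detect outcome-dependent MAR missingness of ILDI, and in the mechanisms tried bias remained only when missingness depended on both ILDI and the outcome. The adaptive-capacity and perception outcomes, and the adoption part of PH5, do not have income as their outcome and are not covered by this point.

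No size can be read from the document. Under the assumptions above, the PH5 slope lost roughly 0.03 to 0.06 of 0.30, and the two-group contrast moved by 0 to 0.12 SD. Other missing rates, withholding patterns or income distributions would give other values. The primary analysis is not invalidated. What lacks support is any reading of agreement as protection against withheld income.

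**What to change.** 1. In the section on missing data, describe the multiple imputation as an alternative estimator under MAR, not a test of MAR.
2. Add a delta-adjusted analysis for PH5 to the planned mice runs. Shift imputed household income, on the scale used in the PH5 model, over a range fixed in advance (for example −0.5 to +0.5 SD), with separate shifts for BEI 0–1 and BEI 2–3. Report the shift at which the PH5 income conclusion changes. In the illustration a shift of about 0.94 SD was needed to undo strong withholding, so consider whether the grid should extend to about ±1 SD.
3. If this is extended to PH2 as a secondary check, shift one imputed income component at a time, on a scale that allows zeros, and recompute ILDI. Multiplying all sources by a common factor leaves every share, and so ILDI, unchanged. Shifting total income alone does not touch ILDI. Log-income is undefined for a source with zero income.

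The cost is modest extra code on imputations already planned and one supplementary table. Analysis is scheduled for 2027, so the range can be fixed before results are seen. The output would parallel the robustness value already planned for confounding.

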Households with multigenerational demographic composition and participation in community organizations (PH3) will report higher adaptive capacity (as measured by the RACI), and this association will be supported by a more diversified portfolio of adaptation strategies (ASDI). This hypothesis is grounded in demo-livelihoods frameworks [32], which emphasize the role of intergenerational structures and social capital in shaping livelihood decisions and adaptive responses.

Secondary outcomes (exploratory measures to enrich analysis):

a) Adaptation Strategy Diversity Index (ASDI): a count-based index capturing the number and variety of adaptation practices reported by each household, including both traditional (e.g., collective work, soil management, water storage) and innovative strategies (e.g., improved seeds, irrigation systems, shade management). This is an author-developed indicator, conceptually grounded in livelihood and adaptation portfolio approaches widely used in climate adaptation research. The index reflects the breadth of a household’s adaptation repertoire, with higher values indicating a more diversified set of responses to climate impacts. The ASDI supports the examination of PH3 by providing a complementary measure of how demographic composition and social capital relate to adaptation strategy diversity.b) Municipal Climate Engagement Typology: a contextual variable (high, medium, or low engagement) constructed from a systematic analysis of municipal climate-related policies and budgets. The typology follows consolidated methodologies [33,34], combining two dimensions: (i) *policy engagement*, assessed through the presence, depth, and quality of municipal adaptation and mitigation plans (including objectives, instruments, and implementation mechanisms); and (ii) *budgetary engagement*, assessed through the classification and quantification of climate-relevant expenditures in municipal budgets. Municipalities are then categorized into high, medium, or low engagement based on their combined policy and budget scores (used to test HP4).

All outcomes will be operationalized on continuous, ordinal, or categorical scales, as appropriate, and incorporated into multilevel linear and generalized linear models (LMM/GLMM), with families (level 1) nested within settlements (level 2), which are nested within municipalities (level 3).

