#### Addressing confounding and sensitivity analysis.

To mitigate potential confounding, the multilevel models will include a rich set of pre-specified covariates at different levels: (1) Household Level (Level 1): Age and education of the household head, household size, gender of the household head, asset index, length of residence in the settlement; (2) Settlement Level (Level 2): Settlement type, distance to the nearest paved road, presence of a producers’ cooperative, years since settlement establishment; (3) Municipality Level (Level 3): Municipal Climate Vulnerability Index (MCVI), Municipal Climate Engagement Typology, and geographic region (e.g., floodplain vs. upland).

Acknowledging the impossibility of measuring all potential confounders, we will conduct a formal sensitivity analysis for the key associations related to our primary hypotheses (e.g., the association between BEI and household income). We will use the sensemakr package in R, following the framework developed by Cinelli and Hazlett (2025) [45]. For each key finding, we will report the Robustness Value (RV), the minimum strength of association (partial $R^{\text{2}}$) that an unmeasured confounder would need to have with both the exposure and the outcome to explain away the observed effect. We will also present contour plots to visualize how the effect estimate and its confidence interval would change under different scenarios of confounding. This will provide readers with a transparent assessment of the robustness of our inferences to unobserved confounding.

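### The imputation sensitivity analysis names a cluster-level method (2lonly) for household-level survey variables, so its comparison with the primary analysis would not be informative

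*Protocol article*

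**What the plan says.** In the Protocol article, section Handling of missing data, the main approach is likelihood-based: "Our primary analysis will use a Full Information Maximum Likelihood (FIML) estimation within the mixed-effects models (lme4 package in R"). Imputation is the check on it: "To assess the robustness, we will conduct sensitivity analyses using Multiple Imputation (mice package in R"). Its scope is wide: "We will create 20 imputed datasets, including all model variables and auxiliary variables correlated with missingness". The method is then fixed: "The multilevel structure will be respected during imputation using the 2lonly method, incorporating cluster means of level 1 variables as predictors". The section ends this part by committing to compare the pooled imputation results with the primary analysis.

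The level of each variable is set elsewhere in the article. Primary and secondary outcomes defines the hierarchy "with families (level 1) nested within settlements (level 2), which are nested within municipalities (level 3"). Addressing confounding and sensitivity analysis lists the household-level covariates: "Age and education of the household head, household size, gender of the household head, asset index, length of residence in the settlement". Operationalization of the indices states that "the BEI will be used primarily as a level-1 predictor (household-level"). No imputation method for household-level variables is named.

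**The concern.** The named method and the variables it has to fill are at different levels. A level-2-only method produces one value per cluster, and cluster means of household variables are the natural predictors for such a target. The sentence's description therefore agrees with the method's name, so this is more than a slip in a label. The gaps that a household survey produces are in income shares, Likert items, assets and education, which differ between families in the same settlement.

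At stake is the value of the robustness check. If every missing household in a settlement receives the same value, the imputed cases carry no information on how families within a settlement differ. PH2, PH3 and PH5 are largely about such differences. A discrepancy from the primary analysis could then be read as sensitivity to missing data when the imputation step created it.

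**Working it through.** The plan gives no figure to reproduce. The check compares levels first and then illustrates the size.

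**1. Which data the sentence governs.** The same section discusses respondent non-response just before it: "Interviewers will be trained to probe for reluctant or “don’t know” responses". The auxiliary variables it names (interview duration, interviewer ID) belong to household interviews. Missing external data get their own rule in a later paragraph. The 2lonly sentence therefore covers the household survey.

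**2. Level of the targets.** Families are level 1. The survey outcomes, the Bioeconomy Engagement Index and the six covariates are family-level. Within the listed covariates, 2lonly suits only those constant within a cluster, such as the four settlement covariates (type, distance to a paved road, cooperative, years since establishment).

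**3. Information lost for an imputed household.** The within-settlement share of variance is 1 − ICC. With the ICCs in Sample justification and statistical power:

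| ICC | 1 − ICC |
|---|---|
| 0.05 | 0.95 |
| 0.10 | 0.90 |
| 0.15 | 0.85 |
| 0.30 | 0.70 |

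**4. Missing outcome, completely at random.** Let *b* be the true within-settlement slope and *p* the fraction missing. Imputed values are constant within a settlement, so they add nothing to the within-settlement covariance with the predictor, and the predictor's variance is unchanged. The expected slope is *b*(1 − *p*). With an assumed *b* = 0.30:

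- *p* = 0.10: 0.30 × 0.90 = 0.27
- *p* = 0.15: 0.30 × 0.85 = 0.255
- *p* = 0.30: 0.30 × 0.70 = 0.21

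A simulation with 30 settlements of 20 families, drawing one value per settlement, gave about 0.27, 0.26 and 0.21 across the protocol's ICCs, in agreement with the formula.

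**5. Missing at random.** In a second simulation (same layout, 20 imputations, 100 replicates per setting), missingness depended on the other variable, at nominal rates of 10%, 20% and 30%. Mean within-settlement slopes over the four ICCs, true value 0.30:

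| Incomplete variable | 10% | 20% | 30% |
|---|---|---|---|
| Outcome, one value per settlement | 0.26–0.27 | 0.22–0.23 | 0.19–0.20 |
| Covariate, one value per settlement | 0.27–0.29 | 0.24–0.28 | 0.22–0.27 |

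Household-level imputation that respected settlement gave 0.29–0.31 in every setting. The attenuation therefore comes from the level of the imputation, not from the missingness.

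**The case against.** The strongest reply is that the sentence is condensed. The imputation covers all model variables, including settlement covariates, and 2lonly with cluster means is right for those. Household-level methods might be set out in the full plan or the scripts. This is possible, but the text presents 2lonly as the way the multilevel structure is respected. The article could have left the method open; it named one that does not fit most of its targets.

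A second reply is that the software may refuse a target only partly missing within a cluster. The analyst would then have to change method, and no misleading result would appear. That stands as a limit: the attenuation figures apply only if the method runs. The planned step still could not be carried out as written.

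Third, the effect is modest when little is missing, and the plan's mandatory field checks and interviewer probing may keep it low. That also stands.

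Four stronger inferences are tempting, and the documents do not support them:

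- **The primary results are compromised.** They are not: imputation is only the sensitivity analysis.
- **Item non-response has no other protection.** The plan makes FIML its primary method for that purpose. Whether FIML in lme4 is adequate is a separate question, and this point does not rest on it.
- **The ICC would be overstated.** With one drawn value per settlement and 15% of the outcome missing, simulated ICCs of 0.051, 0.100, 0.156 and 0.299 fell to 0.048, 0.091, 0.140 and 0.260. A consistent rise appeared only when gaps were filled with the settlement mean without a draw (0.100 to 0.131).
- **Three-level imputation or municipality indicators are required.** With at most two settlements per municipality, settlement carries most of the structure. Municipality indicators would be collinear with the municipal vulnerability index and engagement typology, which the plan also puts in the imputation model.

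**Conclusion.** The concern holds in a limited form: the stated imputation method is at the wrong level for the household variables, and no suitable one is named. If the method runs, associations in the imputed data are pulled toward zero. For a missing outcome, an assumed slope of 0.30 becomes about 0.27 at 10% missing, 0.26 at 15% and 0.21 at 30%; for a missing covariate the loss is generally smaller. If it does not run, the robustness check is not delivered as planned. In either case the comparison with the primary FIML analysis is uninformative or misleading, while the primary estimates themselves are unaffected.

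The sizes rest on assumptions: the true slope, the missingness rates (the documents give none), the missingness mechanism, one drawn value per settlement, and a simple within-settlement slope in place of the full mixed model. The documents do not describe how 2lonly behaves; that reading rests on its name, the plan's own description of its predictors and the usual working of the method. Attenuation appeared in every setting run, and only its size depends on the missingness rate.

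**What to change.** In Handling of missing data, name a level-1 multilevel imputation method for incomplete household variables, matched to type (continuous, binary, ordinal), with settlement as the cluster. State that 2lonly is kept only for incomplete settlement-level covariates. The rest of the imputation plan, including the 20 datasets, the auxiliary variables and the comparison with the primary analysis, can stay.

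This takes about a sentence of text and different imputation functions. The cost is longer run time and convergence checks. Study status and timeline places data analysis in 2027, so the change can be made before any data are analysed.

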#### Data collection methods.

The study employs three complementary data collection methods: household surveys, semi-structured interviews, and focus groups. The household survey captures quantitative information on socioeconomic characteristics, productive activities, climate perceptions, and adaptation practices, using a structured questionnaire administered face-to-face to a randomly selected adult decision-maker in each household.

Qualitative data will be collected through two instruments. First, semi-structured interviews will be conducted with municipal public managers (1–3 per municipality), allowing in-depth exploration of policy implementation challenges, resource constraints, and perceptions of local climate risks. Second, focus groups with community leaders (8–12 participants per settlement) will be used to capture collective experiences, shared vulnerabilities, and community-level adaptation strategies. Both methods are designed to generate rich contextual information that complements survey findings.

Detailed guides for each instrument (survey, interview, and focus group) are provided in the Supplementary Material (S1–S3 Files).

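### The pre-specified models have no interviewer term, so interviewer effects on the CVPS and RACI may be absorbed into settlement or regional differences, depending on an interviewer assignment that the article does not state

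*Protocol article*

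**What the plan says.** Protocol article, Data collection methods: household data are collected "using a structured questionnaire administered face-to-face".

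Handling of missing data: "auxiliary variables correlated with missingness (e.g., interview duration, interviewer ID), will be included in the imputation model". Multiple imputation is itself a sensitivity analysis. The primary analysis is likelihood-based estimation in the mixed models.

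Primary and secondary outcomes: the models nest families in settlements and settlements in municipalities. CVPS (linked to PH1) is an average of 1–5 perception items, and RACI (linked to PH4) an average of 1–5 self-assessment items. Both are primary outcomes.

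Addressing confounding and sensitivity analysis: "the multilevel models will include a rich set of pre-specified covariates at different levels". The household-level list is "Age and education of the household head, household size, gender of the household head, asset index, length of residence in the settlement". The settlement and municipality lists likewise contain no interviewer or field-team variable.

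The article gives no number of interviewers, no rule for assigning them to settlements, and no interviewer variance.

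**The concern.** In a face-to-face survey, interviewers differ in the ratings that they elicit, and attitude items are the most exposed. PH1 sets forest cover against CVPS, and PH4 sets municipal policy against RACI. Both are contrasts between settlements or municipalities, the level at which interviewer effects do harm if interviewers are tied to places.

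Two consequences are possible, and they need different assignments:

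- If each settlement has its own interviewer, interviewer variance adds to settlement variance and power falls.
- If one team covers many settlements in a region, and forest cover or policy also differs by region, a team's rating habits can pass for an exposure effect.

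The article names interviewer ID among variables that may be correlated with missingness, so it already allows that interviewers influence response behaviour. It does not carry this over to the ratings themselves.

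**Working it through.** **Inputs from the article** (Sample justification and statistical power; Table 2): 600 families, 30 settlements, about 20 families each, 5% significance, 80% power. The stated continuous MDE is 0.34 at ICC 0.05 and 0.47 at ICC 0.15.

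**Assumptions:** a two-sided test; a binary settlement-level contrast of 15 v 15 settlements; interviewer variance r = 0.02 to 0.05, relative to a total of 1 and added to it.

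**1. The plan's own figure.** Variance of a settlement mean: v = ICC + (1 − ICC)/20. SE of the contrast = √(2v/15). MDE = 2.90 × SE, where 2.90 is the noncentral-t factor for 80% power on 28 df.

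- ICC 0.05: v = 0.05 + 0.0475 = 0.0975; SE = 0.114; MDE = 0.331 (stated 0.34). Power at 0.34 is 82%.
- ICC 0.15: v = 0.15 + 0.0425 = 0.1925; SE = 0.160; MDE = 0.465 (stated 0.47).

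Both stated values reproduce within 3%.

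**2. Interviewers not shared between settlements, J per settlement, ICC 0.05.** v = 0.0975 + r/J.

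| J | r | v | MDE |
|---|---|---|---|
| 1 | 0.02 | 0.1175 | 0.363 |
| 1 | 0.05 | 0.1475 | 0.407 |
| 2 | 0.02 | 0.1075 | 0.347 |
| 2 | 0.05 | 0.1225 | 0.371 |
| 4 | 0.02 | 0.1025 | 0.339 |
| 4 | 0.05 | 0.1100 | 0.351 |

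With J = 1, the effective ICC is (0.05 + 0.02)/1.02 = 0.069 to (0.05 + 0.05)/1.05 = 0.095, and power at 0.34 falls from 82% to 75–65%.

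**3. Type I error by assignment.** Simulated with no true effect, ICC 0.05, three regions of five municipalities with two settlements each, 10,000 runs per scenario. A settlement-level predictor is tested on settlement means without a municipality level (28 df). A municipality-level predictor is tested on municipality means (13 df). Unless noted, half of the predictor variance lies between regions.

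| Assignment | Settlement-level predictor | Municipality-level predictor |
|---|---|---|
| One interviewer per settlement, r = 0.05 | 5.0% | 4.6% |
| One team per municipality, r = 0.05 | 6.5% | 5.0% |
| Three regional teams, r = 0.02, predictor unrelated to region | 4.8% | 5.2% |
| Three regional teams, r = 0.02 | 11.0% | 9.8% |
| Three regional teams, r = 0.05 | 17.4% | 14.2% |

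The inflation needs both shared teams and an exposure that follows the same gradient.

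**4. Effect of a team term in the regional scenario.** One check with such a term gave about 5–6%. A second, with a team random intercept fitted by REML on settlement means and tested on 28 df (1,500 runs per scenario), gave about 7–9%. With only three levels the team variance is poorly estimated, so the term removes most of the inflation but not necessarily all of it.

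**The case against.** The strongest reply is that this is a journal article. Field rosters and an interviewer variance component commonly sit in a field manual or a full analysis plan, and listing interviewer ID as an example auxiliary variable does not rule out other uses. This stands in part: nothing is contradicted and no stated figure is wrong. But the article sets out the model levels and presents its covariates as pre-specified, and interviewer is in neither. A later analysis plan could add the model term. It could not separate interviewer from settlement if the two coincide in the field.

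The power loss may also be double counted, because the ICCs are partly informed by pilot data and may already contain interviewer variance. Even if they do not, 0.069–0.095 lies inside the article's ICC grid, and 0.36–0.41 lies between Table 2's 0.34 and 0.47. Both points stand. The pilot covered one municipality, however, so it cannot show variance between regional teams.

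A reader might infer that interviewer effects are certainly absorbed into settlements. The documents do not support this, since they give no assignment. With four interviewers per settlement the MDE is 0.34–0.35, practically the stated value.

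A reader might also take type I error to be as high as 9–22%. That range needs six to ten interviewer territories, exposure constant within each, and no municipality level. The article plans a municipality level and does not say that forest cover or policy is constant over such territories. On municipality means the same scenario gives 7–11% at r = 0.02 and 9–17% at r = 0.05. With exposure independent of territory it gives 4.9–5.4%.

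**Conclusion.** The point holds as a conditional risk. Interviewer ID is named only for imputation, and the pre-specified models omit it for two primary outcomes that are face-to-face self-ratings. The size rests on an assumed interviewer variance of 2–5% and on an unstated assignment:

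- **One interviewer per settlement, ICC 0.05:** MDE 0.36–0.41 instead of 0.33, unless the ICCs already include this variance. Type I error is not inflated.
- **Regional teams and a partly regional exposure:** type I error of about 10–17% with a settlement intercept only, somewhat less with a municipality level, and about nominal if exposure is independent of team territory.

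These are alternatives and should not be read as one joint consequence. The planned analysis for unmeasured confounding is no substitute, because interviewer is measured and can be modelled directly.

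**What to change.** - Add a random intercept for interviewer, crossed with settlement, to the CVPS and RACI models, at minimum as a pre-specified sensitivity analysis.
- State how interviewers are assigned. Where more than one existing interviewer visits a settlement, allocate the sampled families among them at random. Where travel allows, avoid tying one interviewer or team to one settlement or region.
- Full rotation across municipalities is optional. The article cites logistical constraints in remote settlements, so rotation cannot be assumed to be cheap.

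The allocation has to be settled for the fieldwork. Where each settlement has its own interviewer who works nowhere else, the added term cannot separate the two or recover the lost power.

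Cost: a field roster and one extra variance component. It will be imprecisely estimated if interviewers are few, and intervals will be slightly wider where interviewers are regional.
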